**Methods/design:**

Using the Health Belief Model as a guide, this randomized controlled trial (RCT) will test the efficacy of four sun protection interventions targeting Operating Engineers: a) education only; b) education and mailed sunscreen; c) education and text message reminders; and, d) education, mailed sunscreen, and text message reminders. Participations in the study will be offered during regularly scheduled safety trainings at the Local 324 Training Center. Pre- and post-intervention surveys will be collected to determine changes in sunscreen use and sun burning, the primary dependent variables. The analyses will include: a) paired t-tests to determine changes over time (from pre-intervention to post–intervention) in outcome variables (sunscreen use and burning) separately in the 4 intervention groups, b) Repeated Measures Analysis of Variance (RM-ANOVA) to compare the changes in outcomes across the 4 groups, and c) t-tests on change scores as follow-ups to the RM-ANOVA to determine exactly which groups differ from each other.

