#### Power analysis

Though limited research has been conducted on interventions to increase use of sunscreen among outdoor workers, a medium sized effect (as defined by Cohen) [28] is plausible based on the studies by Armstrong et al., Buller et al., and Stock et al. [29-31]. Power analysis conducted with PASS software [32] indicated a need for 256 subjects to have 80% power to detect medium sized effects on changes in sunscreen use and sunburn in tests comparing the four individual treatment groups both by tests for mean scores with alpha of .05 two tailed. This sample size will provide even more power for tests of the effects of the interventions over time (pre- versus post- intervention) separately in the four groups.

Based on our prior experience with this group, we expect to approach 460 Operating Engineers of which we expect 15% (n = 70) to be ineligible (e.g., no text messaging or cell phone) and 15% (n = 70) to refuse, allowing for 320 to be consented. Since some analyses will be conducted just on subjects with complete data, this sample size was adjusted to account for a 20% attrition rate found in our previous research on this population resulting in a final sample size of 256. This can easily be done as there are 16,000 Operating Engineers in Local 324 all of which will be eligible and our prior work has estimated that about 23% (3,680) are interested in sun protection interventions [23]. Note, however, that the main analysis will include all subjects following an intent-to-treat approach so will have a larger sample size and thus slightly higher power.

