### Procedures

#### Recruitment, randomization and Pre-intervention survey

Subjects will be recruited while they attend regularly scheduled safety training sessions provided by the Operating Engineers Local 324 Training Center. As has been done in our prior studies, the instructor or research nurse will briefly describe the opportunity to participate in research to the class. Those interested will be provided with an information pack which includes: a) an introductory information letter; b) Informed consent form; and c) the pre-intervention survey. The surveys will have random numbers on them from 1 to 4 assigning subjects to one of the four conditions. Both the study personnel and the subjects will be blinded to the condition of randomization. As requested by leadership at Michigan Local 324, all Operating Engineers, whether they enroll in the study or not, will receive the educational intervention during regularly scheduled training sessions conducted over the winter. Only those that enroll will be randomized, have their data collected, and receive the subsequent interventions during following June, July, and August.

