### Data analysis

Descriptive statistics will be computed for all variables at all measurement times. Distributions will be examined and variables will be transformed to normality if needed. The equivalence of the groups on pretest data will be tested using χ^2^ tests of association for categorical variables and Analysis of Variance (ANOVA) for continuous variables. Then analyses to meet the aim will be conducted by paired t-tests, RM-ANOVA, t-tests comparing change scores and by linear regression analyses. If the groups being compared in the RM-ANOVAs differ on the covariates, the analysis will be changed to repeated measures analysis of covariance (RM-ANCOVA) with the differing covariates controlled. Multiple imputation will be used to replace the values of missing data. An intent-to-treat approach will be used so that subjects are considered to be in the condition to which they were randomized despite how much they actually used that type of care. Analyses will be conducted by two-tailed tests with alpha of .05.

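### The named between-arm tests compare change scores without adjusting for the baseline outcome: valid, but less precise than a baseline-adjusted regression and sensitive to chance baseline imbalance

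*Protocol article*

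**What the plan says.** The Data analysis section names four methods for the aim: "Then analyses to meet the aim will be conducted by paired t-tests, RM-ANOVA, t-tests comparing change scores and by linear regression analyses". The Abstract (Methods/design) gives their roles. Paired t-tests look at change within each arm, RM-ANOVA compares changes across the four arms, and the pairwise step is "t-tests on change scores as follow-ups to the RM-ANOVA to determine exactly which groups differ from each other".

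The Design section provides one survey before the interventions and one after. The Power analysis section is also framed on change: it "indicated a need for 256 subjects to have 80% power to detect medium sized effects on changes in sunscreen use and sunburn".

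Three places bear on adjustment:

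- **Independent variables** names only three arm dummies, with education only as reference.
- **Data analysis** moves from RM-ANOVA to RM-ANCOVA only when arms are found to differ on covariates, and then controls those covariates.
- **The covariate sections** (sun exposure, Health Belief Model, health behaviour, job characteristics) do not list baseline sunscreen use or baseline number of sunburns. These two items appear under Dependent variables.

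The article nowhere states adjustment for the baseline value of the outcome.

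**The concern.** Sunscreen use and sunburns are both asked in the pre-intervention survey, so every participant is meant to have a baseline value of each primary outcome. A change score uses that value in a fixed way: it subtracts all of it, as if the regression of post on pre had slope 1. When the true slope is below 1, this over-corrects, with two consequences.

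- The contrast between arms carries more variance than it needs to.
- If one arm starts worse by chance, regression to the mean makes its change look better. For sunscreen that is the arm with lower baseline use; for sunburn it is the arm with more baseline burns.

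At stake are precision on both primary outcomes and how well a single realised comparison withstands an ordinary baseline imbalance.

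**Working it through.** **Inputs from the article.** Two-sided alpha 0.05 (Power analysis: "tests for mean scores with alpha of .05 two tailed"; Data analysis: "Analyses will be conducted by two-tailed tests with alpha of .05"); 80% power; 256 evaluable; four arms; two surveys.

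**Assumptions.** Equal allocation, so 256/4 = 64 per arm (the ratio is not stated). A medium effect means d = 0.5 in SDs of the change score (the figure 0.5 is not printed). The pre-post correlation r is 0.3, 0.5 or 0.7 (none is given). Scores are roughly normal, which is an approximation for five-category items.

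**1. The plan's own figure.** A two-sample t-test with d = 0.5, alpha 0.05 and power 0.80 needs 63.77, so 64 per arm and 4 × 64 = 256. Power at 64 per arm is 80.1%. With 20% attrition, 256/0.8 = 320, which matches the number to be consented. A four-group ANOVA with f = 0.25 would need only about 179 in total, so the stated size is that of a pairwise comparison.

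**2. The two named between-arm tests are one.** With two time points, the RM-ANOVA group-by-time F equals the one-way ANOVA F on post minus pre. In a simulated data set with four arms of 64, both gave F = 1.2048.

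**3. Precision, equal pre and post variances.** Per-person variance is proportional to 2(1-r) for the change score and 1-r² for the adjusted comparison. The ratio is 2(1-r)/(1-r²) = 2/(1+r). The same true effect has standardised size 0.5 × √(2/(1+r)) under adjustment.

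| r | 2/(1+r) | change-score variance larger by | adjusted d | adjusted power, 64 per arm | total N for 80% |
|---|---|---|---|---|---|
| 0.3 | 1.538 | 54% | 0.620 | 93.6% | 168 |
| 0.5 | 1.333 | 33% | 0.577 | 90.0% | 196 |
| 0.7 | 1.176 | 18% | 0.542 | 86.1% | 220 |

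In 20,000 simulated trials per r, the inverse ratio (adjusted over change score) was 0.66, 0.75 and 0.86, against (1+r)/2 = 0.65, 0.75 and 0.85.

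**4. Precision, unequal variances.** Let k be pre SD over post SD. The ratio becomes (k² + 1 - 2rk)/(1-r²), and power follows from d = 0.5 × √ratio.

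| k (assumed) | r = 0.3 | r = 0.5 | r = 0.7 |
|---|---|---|---|
| 0.75 | 1.1125/0.91 = 1.22; power 87.4% | 0.8125/0.75 = 1.08; 83.2% | 0.5125/0.51 = 1.005; 80.3% |
| 1.25 | 1.8125/0.91 = 1.99; power 97.7% | 1.3125/0.75 = 1.75; 96.0% | 0.8125/0.51 = 1.59; 94.3% |

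The ratio equals 1 only when k = r and is otherwise above 1. Apart from the degree of freedom spent on the covariate, adjustment therefore loses nothing in expected precision.

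**5. Chance imbalance, equal variances.** Given a baseline difference D (in baseline SDs), the change-score contrast shifts by -(1-r)D. The simulated slopes on D were -0.70, -0.50 and -0.30 for change scores and about 0 for the adjusted estimate. The SE of D at 64 per arm is √(2/64) = 0.177. A one-SE imbalance therefore moves the estimate by 0.7 × 0.177 = 0.124, 0.5 × 0.177 = 0.088 or 0.3 × 0.177 = 0.053 baseline SD. The assumed effect of 0.5 change-score SD is 0.5 × √(2(1-r)) = 0.592, 0.500 or 0.387 baseline SD, so the shift is about 21%, 18% or 14% of it.

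**The case against.** The strongest defence is that nothing in the plan is wrong. The analysis matches its power calculation, the sample size reproduces, and both estimators were centred on the true effect in the simulations. This stands. A reader might infer that the planned comparison is biased or the trial underpowered, and the documents support neither. The shift in step 5 is conditional on the allocation that happens to occur and averages to zero over randomisations. The power forgone lies above the stated 80%.

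A second defence is that the regression is already listed and a condensed article need not give every model term. That is fair: a fuller document may include baseline, and one cannot infer that it is excluded. But the article names only arm dummies as independent variables, and it gives the decision on which arms differ to change-score t-tests.

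A third is that RM-ANCOVA could cover the point. It would be too strong to say that it cannot: if a pretest outcome counted as a differing covariate, regressing change on arm and baseline gives the same arm effect as regressing the post score on them. But the covariate sections do not list the pretest outcomes, and adjustment would depend on an observed imbalance.

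A fourth is that the size of the gain is uncertain. This also stands; step 4 shows how far it moves with k.

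A reader might also extend the point to the scale of the outcomes, since the plan says "Distributions will be examined and variables will be transformed to normality if needed". The documents do not carry that far. The sentence is conditional and covers all variables. Low use by about three-quarters of the sample is reported for sun block only, and the Abstract and Background disagree on how many burn at least once. The sunscreen item has verbal categories with no stated numeric scoring. Transformation and ordinal models are separate choices.

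**Conclusion.** The point holds as a matter of efficiency and of robustness to realised imbalance, not of validity. The article fixes change-score comparisons as the between-arm tests and states no adjustment for a baseline it already collects.

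Under equal variances and r between 0.3 and 0.7, the change-score variance is 18% to 54% larger, and adjusted power would be about 86% to 94% instead of 80%. If pre SD is 0.75 of post SD, the excess falls to between 0.5% and 22%; if it is 1.25 times post SD, it rises to between 59% and 99%. These figures also assume equal allocation, roughly normal scores and an effect of 0.5 change-score SD. The direction does not depend on r or k; the size does, and neither is documented. The change is worth making because it costs almost nothing, but the trial does not fail without it.

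**What to change.** In the Data analysis section, make one between-arm analysis primary for each primary outcome: a linear regression of the post-intervention score on the three arm dummies, with the baseline score of the same item as a prespecified covariate whatever imbalance is observed. Take the pairwise arm contrasts from this model. Report RM-ANOVA and change-score t-tests as secondary, and align the Abstract.

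State the numeric scoring of the sunscreen categories alongside, since the regression needs it. The sample size need not change.

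The cost is wording only: the baseline items are already collected, the regression is already listed, and no participant, visit or survey question is added.

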The second half of the session will be used for open discussion with Operating Engineers to address their perceived barriers and opinions about using sunscreen. This will allow for a greater understanding of the specific issues related to sun protection in the target population. By addressing the barriers to sun protection use and identifying strategies to overcome them, the participants are more likely to practice the desired behaviors [38-40].

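### The within-arm paired t-tests ignore the training class in which subjects are recruited and educated, so their standard errors are too small if changes correlate within class (minor, cheap to fix)

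*Protocol article*

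**What the plan says.** Under Recruitment, randomization and Pre-intervention survey, the protocol article says: "Subjects will be recruited while they attend regularly scheduled safety training sessions provided by the Operating Engineers Local 324 Training Center". The same section says that all Operating Engineers, enrolled or not, "will receive the educational intervention during regularly scheduled training sessions conducted over the winter". The description of the education (Education only) adds: "The second half of the session will be used for open discussion with Operating Engineers to address their perceived barriers and opinions about using sunscreen".

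Allocation is individual: "The surveys will have random numbers on them from 1 to 4 assigning subjects to one of the four conditions". Arms are therefore mixed within a class. The article mentions no balancing of arms by class.

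For the analysis, the Data analysis section states: "Then analyses to meet the aim will be conducted by paired t-tests, RM-ANOVA, t-tests comparing change scores and by linear regression analyses". The abstract (Methods/design) specifies "paired t-tests to determine changes over time", applied separately in each of the four arms. Class is not among the covariates listed under Measures. The switch to RM-ANCOVA brings in only covariates on which the groups differ. The Power analysis section uses no design effect and says that the within-arm tests over time will have even more power than the between-arm tests.

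**The concern.** Classmates share a training date, a presenter and a discussion meant to change the behaviour that is later measured. Their changes from baseline may therefore be correlated. A paired t-test has no place for that correlation.

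Within one arm, the class effects do not cancel. They add to the true error of the mean change, while the test computes its standard error as if every subject were independent. The pooled time effect in the RM-ANOVA is exposed more strongly, because it averages over all members of a class and not only the quarter or so in one arm.

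At stake is whether change is declared too readily in individual arms or overall. Every arm receives education, so the within-arm tests are the only planned look at whether education alone is followed by change. The Discussion plans to carry the best interventions into a wider trial, and a spurious within-arm improvement could colour that choice.

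**Working it through.** **Inputs from the protocol article.** 256 completers in four arms, so 256/4 = 64 per arm; 80% power; a medium effect, taken here as a standardised difference of 0.5; two-tailed alpha 0.05; 20% attrition (Power analysis, Data analysis).

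**Inputs assumed.** Completers per class m = 8 to 32, and ICC of the change score 0.01 to 0.10. The article gives neither.

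**Step 1: the plan's own figure.** The two-sample t-test calculation gives 63.8, rounded up to 64 per arm, or 256 in total, with power 80.1%. Allowing for attrition, 256/0.80 = 320. Both stated figures reproduce, under independence.

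**Step 2: within-arm paired t-test.** With four arms allocated freely within classes, a classmate is in the same arm with probability 1/4. The variance of an arm's mean change is therefore inflated by

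DEFF = 1 + ((m − 1)/4) × ICC.

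The true two-sided error rate of a nominal 5% test is about 2 × [1 − Φ(1.96/√DEFF)].

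| m | ICC | DEFF | true SE / reported SE | error rate |
|---|---|---|---|---|
| 8 | 0.01 | 1 + 1.75 × 0.01 = 1.018 | 1.009 | 5.2% |
| 8 | 0.10 | 1 + 1.75 × 0.10 = 1.175 | 1.084 | 7.1% |
| 20 | 0.05 | 1 + 4.75 × 0.05 = 1.238 | 1.112 | 7.8% |
| 32 | 0.01 | 1 + 7.75 × 0.01 = 1.078 | 1.038 | 5.9% |
| 32 | 0.10 | 1 + 7.75 × 0.10 = 1.775 | 1.332 | 14.1% |

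Simulation with free allocation (20,000 runs per setting) agrees: 5.4% (m = 8, ICC 0.01), 7.9% (m = 20, ICC 0.05) and 14.0% (m = 32, ICC 0.10). If arms happened to be balanced within class, DEFF = 1 + (m/4 − 1) × ICC, which is slightly smaller; its maximum here is 1 + 7 × 0.10 = 1.70, an error rate of 13.3%.

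**Step 3: pooled time effect.** Here DEFF = 1 + (m − 1) × ICC. At m = 20 and ICC 0.05 this is 1 + 19 × 0.05 = 1.95, an error rate of about 16%. Over the assumed range it runs from 1.07 (5.8%) to 4.10 (33%).

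**Step 4: between-arm comparisons.** Arms are crossed with class, so the class effect is partly or wholly shared. If arms are balanced within class, the ratio of true to reported SE is √(1 − ICC), for example √0.95 = 0.975, so the test is slightly conservative. In simulation (8,000 runs per setting, m = 8 to 32, ICC 0.02 to 0.10), the error rate was 3.8% to 4.9% with balance and about 5% (4.5% to 5.6%) with free allocation. With balance, a class term would raise power from 81.4% to 82.7% at ICC 0.05 and from 82.0% to 84.6% at ICC 0.10 (normal approximation).

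**Step 5: does the correction work?** Class-robust standard errors with (classes − 1) degrees of freedom gave within-arm error rates of 5.0% to 5.6% in simulation, for 8 to 32 classes and ICC 0.01 to 0.10. A plain random-class model rejected at only 2.2% to 3.9%, so it overcorrects unless a small-sample adjustment is used.

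**The case against.** **The aim is between-arm.** The specific aim concerns differences in change among the four arms, and those tests are sound. The within-arm tests are uncontrolled: a better standard error will not separate intervention from season, weather or regression to the mean. This stands, and it is why the point is minor.

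**The inputs are unknown.** The outcome is self-reported summer behaviour, surveyed by mail in the fall, months after a winter session. The ICC of change could be close to zero, and with small classes or an ICC near 0.01 the effect disappears. This also stands. The range must start at about 5%, and quoting only larger ICCs would mislead.

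**A condensed article with no analysis plan shown.** The regression models are named without their terms, so a class term there cannot be ruled out. That is fair for the regressions. It does not reach the paired t-tests, which are named explicitly and cannot carry such a term.

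**Stronger readings.** A reader might infer that this is in effect a cluster trial, that the between-arm tests are also too liberal, or that 256 needs a design effect. The documents do not support this, since each subject is assigned individually and arms are mixed within classes. Nor does the statement about extra within-arm power fail: at a standardised change of 0.5, within-arm power falls from about 98% to no lower than about 87% (arms balanced within class), still above 80%. The harm is to error rates and confidence intervals.

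**Conclusion.** The point holds as a minor one. The stated within-arm paired t-tests do not fit the stated recruitment and education by class. If the class ICC of the change scores is positive, these tests and the pooled time effect have standard errors that are too small. The within-arm false-positive rate is about 5% to 14% for 8 to 32 completers per class and an ICC of 0.01 to 0.10. Both ranges are assumptions, and the lower end is negligible. The between-arm tests remain valid and the sample size stands.

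**What to change.** Record each subject's training class at enrolment; it may be hard to reconstruct later. Test the within-arm and pooled pre-post changes with class-robust standard errors and degrees of freedom based on the number of classes, or with a class random effect and a small-sample correction.

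The between-arm RM-ANOVA and change-score tests need not be replaced. Adding a class term to them is optional and gains about 1 to 3 points of power at ICC 0.05 to 0.10.

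The cost is one ID variable, a sentence or two in the analysis section and slightly wider within-arm intervals. No extra subjects or visits are needed.

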#### Health belief model covariates

The impact of the intervention on the four components of the Health Belief Model, which have been empirically supported by previous studies, will be measured with questions (rated on a 5-point scale) similar to those used in our tobacco cessation studies [48]. Perceived susceptibility will be measured by the questions: How likely do you think you are to sunburn next summer? and How likely do you think you are to develop skin cancer? Perceived severity will be measured by the questions: How bad would it be for you to get sunburned? and How bad would it be for you to get skin cancer? Perceived benefits to using sun protection will be measured by the question: How important is it that you prevent sun burning? and How important is it that you prevent skin cancer? Perceived barriers will be measured by the question: How difficult will it be to apply sun protection regularly [49,50]?

Several mediators of the Heath Promotion Model will also be measured. Self-efficacy will be measured by the question: How confident are you that you can apply sun protection regularly? Cues to action, which will vary depending on the intervention to which subjects were randomized, will be measured by the question: The educational presentation and/or mailed sunscreen and/or text message reminders increased the likelihood that I will use sunscreen.

Psychological status will be measured using the well validated Center for Epidemiologic Studies/Depressed Mood Scale (CES-D-SF) [51]. Since medical comorbidities can increase health motivation, comorbidities will be measured using a validated self-report instrument [52]. Since demographic factors may mediate sun protection behaviors, age, sex, ethnicity/race, educational level, marital, and veteran status will be asked.

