#### Health behavior covariates

Since poor health habits have been shown to cluster together [53-55] and our prior research has shown that problem drinking, greater body mass index (BMI) and greater physical activity levels predict use of sunscreen and/or sun burning [23], questions will be asked about other health behaviors including smoking (Heavy Smoking Index) [56], problem drinking (Alcohol Use Disorders Identification Test-Hepatitis C: AUDIT-C) [57], diet (two questions on fruit and vegetable intake from the validated Willett food frequency questionnaire) [58], a validated physical activity questionnaire [59], and Medical Outcomes Study sleep quality survey [60]. Self-reported height and weight will be used to determine BMI (weight in kilograms divided by the square of height in meters).

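### Covariate adjustment of the between-arm RM-ANOVA is triggered by significance tests of chance pretest differences, so covariates are selected without regard to prognosis

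*Protocol article*

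**What the plan says.** The Data analysis section of the protocol article sets out a two-step rule. First, "The equivalence of the groups on pretest data will be tested", by χ² tests for categorical variables and ANOVA for continuous ones. Then: "If the groups being compared in the RM-ANOVAs differ on the covariates, the analysis will be changed to repeated measures analysis of covariance", "with the differing covariates controlled". The only significance level given is in the same section: "Analyses will be conducted by two-tailed tests with alpha of .05".

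The abstract gives the purpose of the RM-ANOVA: "to compare the changes in outcomes across the 4 groups". Change-score t-tests follow it to locate the differences. The rule therefore governs the omnibus between-arm comparison that serves the specific aim.

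The candidate pool is everything that the Measures section labels a covariate: sun exposure, Health Belief Model, health behaviour and job characteristics. No member is named in advance for the model. Yet under Health behavior covariates the article reports that, in the team's earlier research, problem drinking, "greater body mass index (BMI) and greater physical activity levels predict use of sunscreen and/or sun burning".

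Under Health belief model covariates, the items are also described as measuring "The impact of the intervention on the four components of the Health Belief Model".

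**The concern.** Allocation is by random number, so apart from a fault in randomisation any pretest difference between arms is chance. A p-value for imbalance does not show whether a variable is related to the outcome. A rule based on it lets irrelevant variables in when they happen to be imbalanced and keeps useful predictors out when they happen to be balanced.

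Two things are at stake. The form of the between-arm model, adjusted or not and for what, cannot be known until the pretest data have been tested. And precision available from predictors the team already knows about would usually go unused, in a trial sized at about 80% power for pairwise contrasts.

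There are two smaller matters. The switch is stated for the RM-ANOVA and not for the follow-up change-score t-tests, so the omnibus and pairwise results could rest on different models. And the covariate pool contains Health Belief Model items that the interventions are designed to move, with no statement of which time point may be adjusted for.

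**Working it through.** **The plan's own figure.** The Power analysis section gives 256 subjects for 80% power, a medium effect and two-sided alpha .05. With d = 0.5, a two-sample t-test needs 63.8, so 64 per arm; 4 × 64 = 256, with pairwise power 0.801. Allowing for 20% attrition, 256 / 0.80 = 320. Both stated numbers are reproduced. Equal arms are assumed below.

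**Size of the pool.** Counting from the Measures section:

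| Group | Every item | Composites, checklists left out |
|---|---|---|
| Sun exposure | 4 | 4 |
| Health Belief Model and self-efficacy | 8 | 5 |
| Mood, comorbidity | 2 | 2 |
| Demographic | 6 | 6 |
| Health behaviour | 7 | 6 |
| Job (work type, cab, cab open, region) | 7 | 4 |
| Protective equipment | 8 | – |
| Occupational exposures | 9 | – |
| **Total** | **51** | **27** |

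The cues-to-action item is left out of both columns because it can be answered only after the intervention.

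**How often the switch fires.** With k tests at .05 and no true differences, the expected number of false differences is 0.05k. If the tests are independent, P(at least one) = 1 − 0.95^k.

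- k = 27: expected 1.35; 1 − 0.95^27 = 0.750.
- k = 51: expected 2.55; 1 − 0.95^51 = 0.927.
- If correlation leaves the equivalent of 20 tests: 1 − 0.95^20 = 0.642.
- At least one baseline Health Belief Model variable qualifies: 1 − 0.95^5 = 0.226 by construct, 1 − 0.95^8 = 0.337 by item.

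Any one named predictor qualifies with probability of about 0.05, however prognostic it is.

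**Consequence for error and power.** Simulation of 4 arms × 64, 8,000 runs per setting, omnibus F-test on the change score, with one covariate having assumed correlation r with the change. For power, one arm is shifted by 0.5 SD.

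| r | Type I, gated | Type I, prespecified | Power, gated | Power, prespecified |
|---|---|---|---|---|
| 0.3 | 0.049 | 0.048 | 0.84 | 0.87 |
| 0.5 | 0.048 | 0.051 | 0.84 | 0.93 |
| 0.7 | 0.035 | 0.048 | 0.83 | 0.99 |

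As a check by the noncentral F distribution: the means 0, 0, 0, 0.5 give noncentrality 64 × (3 × 0.125² + 0.375²) = 12 and unadjusted power 0.834. Adjustment divides the noncentrality by (1 − r²). That gives power 0.838 at r = 0.1 and 0.850 at r = 0.2, so the gain is negligible when r is small. The documents give no value of r.

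**Role of the baseline outcome.** RM-ANOVA with two time points tests change, and the pretest score is already one of its repeated measures. If pre and post variances are both σ² with correlation ρ, the change score has variance 2σ²(1 − ρ), while ANCOVA of the post score on the pretest leaves σ²(1 − ρ²). The ratio is (1 + ρ)/2: 0.65, 0.75 and 0.85 for assumed ρ of 0.3, 0.5 and 0.7. This gain does not depend on any other covariate.

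**The case against.** The strongest defence is that the rule does little damage. Type I error stays at or below nominal in the simulation, and gated power of 0.83 to 0.84 is above the planned 80%. The group-by-time test is a test of change, so a stable predictor that acts equally before and after largely cancels. The article says that drinking, BMI and activity predict use or burning, not that they predict change. All of this stands. It limits the harm but does not justify selecting covariates by imbalance.

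The count can also be challenged: treating each checklist item as a gated covariate is generous, and independence is assumed. That is why a range is given, and why near-certainty of a trigger should not be claimed.

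It can further be said that RM-ANOVA is not called primary and that covariates in the separately listed linear regressions are not described. Both are true, and the point is therefore confined to the RM-ANOVA and its stated rule.

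A reader might infer three stronger claims that the article does not support:

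- **That the covariate set will differ between sunscreen use and sunburn.** The gate compares arms, and both outcomes share the same arms and participants.
- **That it will differ between pairs of arms.** The RM-ANOVA spans all four groups, and the switch is not stated for the follow-up t-tests.
- **That adjusting for Health Belief Model items will remove part of the effect.** The gate works on pretest data, and adjusting for a baseline value does not do that. Only follow-up values would, and the article does not say they will be used.

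**Conclusion.** The concern holds in limited form. The article states a rule under which covariates in its between-arm RM-ANOVA are chosen by chance imbalance. Under independence the switch fires with probability 75% to 93% for 27 to 51 tests, or 64% for an effective 20, while each known predictor is used about 5% of the time. These figures rest on sound randomisation, on .05 applying to the pretest tests, and on the counts shown.

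The effect is on prespecification and efficiency, not on validity: there is no inflation of type I error. The lost precision cannot be sized from the document. In the settings examined it runs from almost nothing (r = 0.1) to a drop from 0.99 to 0.83 in omnibus power (r = 0.7). The time point of the Health Belief Model covariates is an ambiguity to close, not a demonstrated bias. The change is worth making because it is nearly free.

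**What to change.** In the Data analysis section:

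1. Keep the pretest comparison of arms as description only, and delete the significance-triggered switch to RM-ANCOVA.
2. Analyse the post-intervention score by ANCOVA with arm, the baseline value of that outcome, and a short set of baseline covariates named in advance. The predictors the article itself cites (problem drinking, BMI, physical activity) are a natural example. The baseline outcome cannot simply be added to the RM-ANOVA, which already uses it as a repeated measure; hence the change of model.
3. Use this same model for the omnibus test and the follow-up pairwise comparisons.
4. State that post-intervention Health Belief Model values, including the cues-to-action item, are not covariates in the efficacy model and belong to mediation analysis. Baseline values need not be barred.

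The variables named are already in the survey, and the sample size of 256 stands. The cost is revised wording and a few degrees of freedom.
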